### **5.1. SCREENING AND ELIGIBILITY OF PARTICIPANTS**

Each category of participants is governed by its own inclusion criteria and screening procedures:

- 1) Program-level Participants: The BRIDGE intervention is meant to be implemented under the scope of regular trust point activities, therefore, there is no formalized screening or enrollment process. Because we will not be collecting any identifiable study data on these program level participants, we will be applying for a waiver of consent.

## **6. CONFIDENTIALITY OF STUDY DATA**

Human subjects' protection and data safety remain an utmost priority. The primary risks are (1) psychological discomfort and/or distress arising from the personal and potentially sensitive nature of information elicited during assessments; and (2) loss of confidentiality. The level and probability of experiencing such risks are minimal, and the monitoring plan described below is commensurate with these risks. There will be ongoing monitoring of the conduct of the trial to ensure that there are no undue risks to participants, and the data are being collected in a valid and reliable way. In addition, Drs. [name], [name], and the project director are directly responsible for monitoring the security of the data and the safety of participants. Approval will be received from the Columbia University IRB and the Ethics Committee of the Kazakhstan School of Public Health prior to the start of the study.

Safeguarding the confidentiality of personal data reported in screening questionnaires will be achieved via use of instruments that do not contain identifying information as defined by the Health Insurance Portability and Accountability Act (HIPAA).

RAs will verify that all screening instruments and answer sheets are gathered before they leave the data collection site. Safeguarding of program-level primary outcome data on TP clients collected through recruitment coupons and service referral vouchers will use anonymous alphanumeric codes that are not linked to any client data and will be used to generate summary statistics on overall number of TP clients recruited and number of HIV positive clients linked to HIV Care Clinics.

All hardcopy items with identifying information (e.g. brief contact information collected during screening, locator forms, biotesting release form required by the AIDS Center) will be kept in a locked file cabinet in the Project Director's office. All software files with identifying information will be stored on a computer protected by passwords and a firewall; backup copies of files will be encrypted and password protected using 128-bit AES encryption before being archived in a locked file cabinet in the Project Director's office.

### **Data Management Systems to Preserve Confidentiality**

Data management activities and procedures will utilize the electronic data management systems designed by GHRCCA's investigative team to enhance the efficiency, security, and integrity of study data (including QA data), which includes: (1) using a secure and confidential World Wide Web address; (2) scheduling information for RAs, (3) automatically generating summary reports for the Project Director to tailor and Site Project Directors' participation efforts to maximize efficiency, (4) uploading of digitally-recorded and encrypted interviews for QA protocols; (4) collecting, monitoring, and summary reporting of data relevant to day-to-day operations of the study

(e.g., petty cash disbursements); and (5) using a custom-programmed data entry software to ensure consistency, integrity, and security/confidentiality of the transfer of data recorded by interviewers into a computer database. The staff will be trained to use this system by the Project Director.

Due to the need for frequent, long-distance communication, we plan to use internet-based protocols to handle international communications (e.g., Skype conference meetings, e-mails) in a cost-effective manner. We recognize that this carries inherent risks due to the number and frequency of security threats of internet-based protocols. As part of the data management training, all research staff will be informed and trained not to use any identifying information in such communications. If such information must be transmitted, it will be entered into a software file (e.g., word processing or spreadsheet document) and encrypted before electronic transmission. In addition, every effort will be made to use the more secure available method/protocol for all electronic transmissions.

We anticipate using internet-based protocols for transfer of information both regionally as well as between the study and U.S. sites. For example, file transfer protocols (FTP) will be used by study staff to transfer and transmit digital audio recordings for QA purposes. To ensure confidentiality of electronically transferred files, all files will be scrambled using 128-bit AES encryption before upload/transfer via the Internet. Files are transferred for storage on a dedicated server maintained by and accessible only to study staff. Centrally storing all software files on a password- and firewall-protected computer enhances security (e.g., all attempted accesses, whether successful or unsuccessful, are automatically logged and reviewed weekly by a dedicated SIG computer support staff member) and integrity (e.g., automatic backup of encrypted recordings onto optical media) is maintained.

At the completion of the study, all digital files with identifying information will be destroyed using software that meets DoD 5220.22-M specifications for files on magnetic media, overwriting files stored on the flash memory used by digital recorders, and physically shredded for files stored on CD/DVD media. The Project Director has extensive experience with the system and will successfully use it for this application.

These confidentiality procedures have been successfully used in prior health service research in low resource international harm reduction settings, including in other studies conducted in Kazakhstan and Central Asia. We will explain these confidentiality procedures during informed consent to potential participants.

### Responsibilities

The field and analytic staff for the study, as well as the investigative staff, are responsible for immediately notifying the Project Director and PIs and completing incident reports on any breaches of protocol, breakdowns in the consent process, violations of confidentiality of the data, complaints by participants or any serious problems or adverse events. Site Project Director will be responsible for the daily management of data and for ensuring that all study staff adhere to human subjects guidelines. Oversight of data management, including data collection and storage, security, tracking, data analysis software and hardware, and QA will be the responsibility of Drs. [name], [name], [name] and the Site Project Directors who will also be responsible for ensuring that all study staff adhere to human subjects/IRB guidelines.

## **7. POTENTIAL RISKS**

### *7.1. RISKS TO PARTICIPANTS FROM STUDY COMPONENTS*

#### Risks from BRIDGE Intervention activities

The SNS, CRT and ARTAS components of the intervention may produce psychological stress. Efforts will be made to minimize this stress by assuring that well-trained and supervised TP staff will conduct BRIDGE activities. Informed consent will be waived for this portion of the study, however, before taking part in any BRIDGE activities, clients are informed that they have the right to decline to participate in any of the exercises or withdraw at any time during the intervention. Study staff will be trained in the importance of confidentiality, sign confidentiality forms, and will be certified as trained in protecting human participants in research. All TP staff delivering BRIDGE will complete a rigorous, standardized training program, and they will undergo

periodic quality assurance checks to ensure fidelity of the interventions.

#### Risks from HIV Testing

Social discrimination, stigma, and a loss of jobs or housing could occur if someone else learns about a participant's HIV positive rapid test results during the CTR component of Bridge. Receiving an HIV positive rapid test result may produce psychological stress. Study staff and nurses will be trained to provide standard post-test counseling when participants return for positive HIV test results.

### *7.2. ADDRESSING OTHER RISKS TO PARTICIPANTS*

#### Managing Psychological Discomfort

Participants may experience anxiety or discomfort during data collection procedures. Procedures for minimizing risk to participants include the careful selection, training, and supervision of research staff together with the systematic preparation of program participants. These selection, training, and oversight protocols, which have been used in all of the prior research conducted by the investigators, have conferred an ability to answer questions that may arise. At the end of the assessment/intervention session, the research staff will ask anxious or troubled participants for permission to discuss the discomfort with the Project Director. Only with permission of the subject will the research staff discuss the subject's concerns.

Participants may become embarrassed by self-disclosed information shared during interviews. In order to reduce the risk of embarrassment and discrimination, confidentiality norms will be reviewed with research staff, and safeguards for protecting confidentiality of questionnaires and other data as outlined below will be strictly enforced.

Participants at any point during the study may request that their data be destroyed without question. In addition, participants will be reminded that they have the option to skip questions and/or entire instruments.

#### Managing Respondent Distress

All study staff will be trained and reminded to observe verbal and non-verbal signs that may indicate that a participant is emotionally distressed. In cases where a participant is exhibiting distress, the staff member will acknowledge that the questions and activities can raise troubling issues for participants and ask if they want to take a brief break from the activity. At the end of all screening and CASI interviews, whether or not complete, RAs will ask anxious or troubled participants for permission to discuss their discomfort with the Site Project Director. Acute emergency distress referrals will be directed to the appropriate agency (e.g., hospital, mental health center) and the PI and Co-Investigators will be alerted.

#### Handling suicidality, homicidality, intimate partner violence (IPV) and childhood abuse:

There is no law currently in Kazakhstan that mandates researchers or clinicians to report child abuse or neglect, IPV, suicidality, or homicidality. However, if a participant indicates intent to kill or seriously injure another person or suicidal intent or if a participant indicates he or she is neglecting or abusing a child, confidentiality may not be maintained. During informed consent, participants will be apprised of these specific instances where confidentiality may not be maintained. Following protocols used in prior SIG studies with populations at elevated risk for HIV transmission, the Project Director in Kazakhstan in consultation with [name] and the site coordinator will inform the appropriate agency (e.g., law enforcement or hospital). In the case of a suicidal participant, the Site Project Director will immediately accompany the participant to the hospital emergency room or a psychiatrist where he or she can be fully evaluated and will make follow-up referrals. If a participant discloses that he or she is experiencing IPV, we will assess frequency and severity of IPV, conduct safety assessment and safety planning, and provide referrals to appropriate services following a protocol that we have used other studies conducted in Kazakhstan. All incidents where staff identify participants who are involved in child abuse, IPV, or have suicidal or homicidal intent, will be reported immediately to [name] and the Project Director who will be trained to assess whether these incidents may be adverse events and should be reported to the IRB. These incidents will be reviewed and discussed in the investigative team biweekly internet conference meetings.

#### Handling Confidentiality Issues and Cases Where There is Risk of "Imminent Harm"

Staff will be trained to report cases of child abuse or neglect and "imminent harm" to self or others to appropriate

authorities. Participants will be advised during informed consent that study staff will not be able to maintain confidentiality in cases where “imminent harm” to self or others or child abuse/neglect is suspected. If the program staff has evidence that a participant is of “imminent harm” to him/herself, the Project Director will conduct a suicidal assessment. If the Project Director assesses that the person is suicidal, s/he will notify the nurse over our study in the city where it is being conducted and that nurse will arrange for emergency psychiatric evaluation and care. If the TP staff has credible evidence that a participant is of “imminent harm” to others, the Site Project Director will notify the Medical Director and/or the local police depending on the nature and severity of the threat. Similarly, if the study staff has evidence that a participant is endangering the welfare of a child, the Site Project Director will notify the police. If a participant discloses that he or she is experiencing IPV, the Site Project Director will assess frequency and severity of IPV, conduct safety assessment and safety planning, and provide referrals to appropriate services following a protocol that we have used in other studies on HIV prevention. All incidents where staff identify participants who are suspected of child abuse or IPV or who have expressed suicidal or homicidal intent will be reported immediately to the Project Director and the PI, who will assess whether these incidents may be adverse events and should be reported to the IRBs of record and NIH. These incidents will be reviewed and discussed in the investigative team biweekly Skype internet conference meetings.

#### Providing Referrals for Respondents

If a TP study program staff observes signs of distress while working with clients, s/he will ask the respondent if s/he would like to discuss the issues further with appropriate professional service providers. In addition, at the end of the assessments, regardless of whether signs of distress were observed during the interview, the research assistants will ask participants how they are feeling. After allowing the participant an opportunity to express feelings raised by the interview, the interviewer will ask the respondent if s/he would like to discuss the issues further with appropriate professional service providers.

The staff member will offer the respondent a range of service options in the local community. S/he will also offer to assist the respondent in locating appropriate services and will provide enhanced referrals (e.g., calling the organization and assist in making an appointment). If the respondent is undecided about needing help and is not ready to consider a referral at the time of the interview, the interviewer will give her/him a card with the phone number and encourage the participant to contact the Site Project Director, if s/he decides that s/he would like a referral in the future. The total time spent providing referrals will be recorded as will the various types (IPV, mental health, etc.) and methods (general, enhanced) of referrals provided. Participants’ responses to the referral will be assessed at all follow up measures to examine any potential impact of these referrals on primary outcomes. The investigative team has successfully used these procedures other studies.

Similar to the procedures for referrals, data regarding implementation of procedures to address suicidal/homicidal participants will be collected and analyzed in a parallel manner to investigate the effects of the research process itself on utilization/involvement with the service system and other outcomes.

#### Disclosure Protocol:

By virtue of the study population, it is anticipated that some of the subjects may disclose past or current engagement in lawbreaking activity (e.g., sex trading, selling drugs, theft, etc.). Following protocols used in the other studies in Kazakhstan with PWID, research staff and TP providers will inform TP clients of the limits of confidentiality at the start of session. TP staff will not release any information about a TP client and research study staff will not release information on any participants to anyone. The only exception is, as described above, when there is a possibility of “imminent harm to self or others” and/or, through group or individual discussions it becomes clear that a child is in danger or is experiencing physical abuse or neglect.

## **8. ADVERSE EVENTS**

### *8.1. DEFINITION OF ADVERSE EVENTS*

Serious adverse events include death, a life-threatening event, or an event resulting in hospitalization, prolongation of hospitalization, disability, and (re-)incarceration. Serious adverse events, regardless of whether or

not they are study-related, will be reported to the Columbia University IRB and the IRB at the study site serving the participant. Other adverse events include breaches of confidentiality (both intentional – e.g., mandated reporting of suicidal/homicidal participants – and unintentional), and non-life threatening psychological distress, arrest by the police and violence. Drs. [name] and [name] will closely monitor adverse events. The investigative team is aware that the study sample is likely to experience some adverse events, though unlikely to be study-related, due to their vulnerable status in Kazakhstani society, their current or past history of law-breaking behavior (e.g. engaging in sex work) and the high levels of service needs noted earlier in this application. There is a possibility that agreements with police and service providers related to confidentiality are breached, and in this case a severe adverse event (loss of confidentiality and possible arrest of inability to obtain treatment due to arrest, for example) may occur. Drawing upon past and ongoing SIG/GHRCCA studies, the investigative team designed two forms – (1) Adverse Event: Initial Report, and (2) Adverse Event: Full Report – to document adverse events, staff responses and disposition. The procedures used to track, report, and examine adverse events are described below.

## *8.2. PROCEDURES FOR MANAGING ADVERSE EVENTS*

### Protocol to Handle Each Adverse Event

Study staff will identify, manage and document all adverse events. These events may be identified by RAs, the Project Director, Site Project Directors, or other project staff, including QA staff reviewing audio recordings of interviews, or they may be reported by participants. The following steps will be used to monitor, track, and document procedures used to address each adverse event and subsequent disposition:

- 1) Within 12 hours of an adverse event being reported/detected, the study staff member who identified the event will complete a Negative Incident Report form. The report form will include date, description of the event, duration, severity, measures taken to ameliorate the adverse event, and disposition- related information (e.g., time spent providing referrals and type of referral (domestic violence shelter or mental health treatment, etc.). The report form will be reviewed and signed by the Project Director and [name], who will be responsible for ensuring that appropriate actions have been taken.
- 2) Within 24 hours of the adverse event, the research staff member who identified the adverse event will discuss the event and response with the Project Director and the PI in order to ensure adherence to the protocol for handling the event.
- 3) Within 48 hours of the adverse event, [name], after consulting with the Project Director and any involved staff, will ascertain whether the event was related to participation in the study. A Serious Adverse Event reporting form will be completed by [name]. This full report will contain an attached copy of the initial adverse event form, a summary of information obtained from other documentation, sources that clarify the nature of the event and outcomes, and the determination of whether the event was study related and by what criteria such determination was made.
- 4) [name] and the Project Director will be responsible for reviewing the event occurrence with the appropriate staff to ensure that an adequate response is provided to the participant. This will be followed by submission of the full report to the IRBs at Columbia University and the Kazakhstan School of Public Health in Kazakhstan. In the event that a participant withdraws from the study or the investigator decides to discontinue a participant due to an adverse event, the participant will be monitored by the Project Director and the PI via ongoing status assessment until (a) a resolution is reached (i.e. a problem requiring hospitalization is stabilized with no further change expected), or (b) the event is determined to be unrelated to the study intervention.

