#### Compensation (by category of participants listed above)

- 1) PWID program participants in the four cities receive no compensation for taking part in BRIDGE activities, as this is an implementation study. BRIDGE is designed to for trust points to provide it under their normal scope of activities. The one exception is peer recruitment: PWID who become BRIDGE peer recruiters will receive \$2 compensation for every participant successfully referred to the trust point for HIV rapid testing (up to a maximum of \$40), and an additional \$2 for filling out a brief survey when they initially register their coupon numbers with the trust point nurse. This compensation will be provided and monitored by the local project team, but distributed by the trust point nurses. No incentives are given for testing or participation in the study intervention ARTAS sessions.

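### Section 8.2, step 4(b) lets monitoring of participants who leave because of an adverse event end on a narrower relatedness test than step 3 applies

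*Combined protocol and SAP*

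**What the plan says.** Section 8.2 (Protocol to Handle Each Adverse Event) sets out four steps. In step 3, within 48 hours, the person assigned to the task "will ascertain whether the event was related to participation in the study", and the full report must contain "the determination of whether the event was study related and by what criteria such determination was made".

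Step 4 requires an adequate response to the participant and submission of the full report to both IRBs. It then adds a monitoring rule for one group only: participants who withdraw, or whom the investigator discontinues, because of an adverse event. The Project Director and the PI keep assessing these people until one of two conditions is met. Condition (a) is resolution. Condition (b) is "b) the event is determined to be unrelated to the study intervention". The two are joined by *or*.

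Other sections bear on what the intervention is and where harm may arise:

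- Section 2.1 builds BRIDGE from three components: SNS, CTR and ARTAS. Section 7.1 repeats this when it lists intervention risks: "The SNS, CRT and ARTAS components of the intervention may produce psychological stress" (CRT is evidently CTR misprinted).
- Section 3.8 (Compensation) uses the same phrase as 4(b) for one of these components: "No incentives are given for testing or participation in the study intervention ARTAS sessions".
- Section 6 names the primary risks of the study as "psychological discomfort and/or distress arising from the personal and potentially sensitive nature of information elicited during assessments; and (2) loss of confidentiality".
- Section 8.1 counts confidentiality breaches and psychological distress among adverse events.

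**The concern.** The test that classifies an event and the test that may end a person's monitoring are worded differently, and the second is narrower. A study can harm someone through its data collection or data handling without the intervention having any part in it. Section 6 puts distress from assessments and loss of confidentiality first among the risks, so this kind of harm is one the protocol itself foresees.

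If 4(b) is applied as written, a participant who leaves because of such a harm could stop being followed before it has resolved, even though step 3 has attributed the harm to the study. What is at stake is the follow-up of individuals, not any estimate or test in the effectiveness analysis.

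**Working it through.** No sample size, error rate or event rate enters, so the check compares wording and adds one piece of calendar arithmetic.

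**1. The two tests side by side**

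| | Step 3 | Step 4(b) |
|---|---|---|
| Standard | relation to taking part in the study | relation to the study intervention |
| When | within 48 hours of the event | end-point of continuing monitoring |
| Who decides | an assigned person, after consultation | not stated |
| Criteria recorded | yes, in the full report | not stated |

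**2. Does the protocol treat the two standards as the same thing?** Not in its structure. Section 2 says that the study has three main components and that the intervention is the first of them. Section 7.1 covers risks from intervention activities and HIV testing. Section 7.2, on other risks, separately covers anxiety or discomfort during data collection. Nothing in sections 7 or 8 equates the two phrases.

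**3. A test case.** Take an unresolved harm caused by study data collection or data handling, not by SNS, CTR or ARTAS, in a participant who withdrew because of it.

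- Step 3: related to taking part in the study, so study-related.
- Step 4(a): not met, because the harm is unresolved.
- Step 4(b) as written: met, because the intervention did not cause it.
- Since *or* joins (a) and (b), monitoring may stop.

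If 4(b) used the step 3 standard, it would not be met and monitoring would continue until resolution.

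**4. Can the case arise on the stated schedule?** AppSheet collection starts in November 2016, which is month 13 (section 3.3; Appendix A, Post-Implementation Survey). Section 2.2 starts BRIDGE in months 22, 28 and 34. Data collection without the intervention therefore lasts:

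- first site: 22 − 13 = 9 months
- second site: 28 − 13 = 15 months
- third site: 34 − 13 = 21 months

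In these periods a study-caused harm to a client at that site would ordinarily be unrelated to the intervention, because the intervention is not yet running there. Condition 4(b) would then be met automatically on its literal wording.

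**5. Does another rule require follow-up to resolution?** None found. Step 4's response and reporting duties set no such end-point. The two-monthly review looks for trends across all events. Step 4 is the only place in section 8 with an individual monitoring rule and a stopping condition.

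**The case against.** The strongest reply is that 4(b) simply points back to step 3. Section 8.2 assigns only one relatedness determination; no one is asked to make a second, intervention-only one, and no form or criteria exist for it. Section 8 is loose with its labels, and the use in section 3.8 is incidental rather than a definition. This is plausible, and the authors may well have meant one standard. It does not cure the text. Step 3 is fixed within 48 hours, 4(b) is an end-point that can be reached later, and the words in 4(b) name something narrower.

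The second reply is that few study procedures in this protocol could cause the harm. That largely stands. A reader might infer from section 8.2's "including QA staff reviewing audio recordings of interviews" and section 6's "All hardcopy items with identifying information (e.g. brief contact information collected during screening, locator forms" that client interviews, screening and locator records are a substantial source of harm. The documents do not support that. Section 5.1 says program-level participants have no formal screening or enrolment and give no identifiable study data, and they are the only category set out in section 3.8. Table 2 lists process measures, staff CFIR surveys, AppSheet and AIDS Center reports, with no client interview or locator form.

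AppSheet itself is modest: a survey of about 5 minutes on services received, with no identifiers. The list linking its IDs to trust point codes joins one code to another and stays in a locked cabinet. Some more sensitive contacts also fall within the intervention. The peer recruiter survey belongs to SNS and a rapid-test result to CTR, so harms from these would not meet 4(b).

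The third reply is that other protections remain: appropriate action under step 1, an adequate response and IRB reports under step 4, and, in section 7.2, offered referrals and emergency escort for suicidal participants. These are real and apply whatever 4(b) says, but none requires following a person until the harm resolves.

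**Conclusion.** The point stands as a minor participant-safety wording correction. Read literally, 4(b) can release from monitoring a person whose unresolved harm step 3 has attributed to the study.

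A reader might infer more: that any study-caused harm can be closed, that all participants with adverse events are exposed, or that the sponsor meant to narrow the duty. The documents support none of these. The clause governs only participants who withdraw or are discontinued because of an adverse event. It ends one continuing assessment and leaves reporting and response duties in place. Nothing shows that the difference in wording was deliberate.

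The number affected is likely small, but the documents give no adverse-event counts or rates, so no figure can be attached. The effectiveness analysis is not affected. The conclusion assumes that 4(b) is applied as written, that the intervention means SNS, CTR and ARTAS, and, for the 9 to 21 months, that roll-out follows the stated schedule. Confidence is medium, because the single-standard reading is plausible.

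**What to change.** In section 8.2, step 4(b), replace the reference to the study intervention so that the condition reads: *unrelated to participation in the study (the step 3 determination, or a documented later revision of it)*. The parenthesis ties the stopping rule to the determination already made, and allows it to change if better information comes in after 48 hours.

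No new form field is needed for the step 3 determination, because the full report already records it with its criteria; a later revision needs only a dated note. The cost is one phrase in the protocol, and a few events may stay open longer. If the authors always meant one standard, the edit only states their intent.
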